### Data collection and procedures

A detailed overview of measures by informant and timepoint is provided in Fig 1 (SPIRIT schedule). All standardized pretest and posttest measures have demonstrated good psychometric properties. The diary items were adapted from validated instruments (e.g., PANAS-C, externalizing spectrum scales, parent-child relationships [29–32]) and tailored for daily use in young children. While validation of daily diary in early childhood is still emerging, this study contributes to ongoing efforts to evaluate ILD methods in child intervention research.

Data collection spans three phases: pre-intervention (T1), intervention, and post-intervention (T2). During T1 (September 2025), parents and teachers complete online questionnaires. The home visit includes child assent, a brief emotion regulation task, and setup of the m-Path app. From the baseline period through the 18-week intervention and one-week follow-up, daily digital assessments will be completed jointly by parent and child each evening, focusing on emotions, behaviors, and family interactions. To encourage consistent participation, families can earn up to €50 per family as incentives, distributed across key milestones: €10 for completing the pretest questionnaires, approximately €25 for daily questionnaire completion during the study period (with €0.15 per completed daily questionnaire), and €15 for completing the posttest questionnaires. Participation progress is tracked via the m-Path app, and payments will be made after study completion based on participation levels.

The study procedure has been approved by the Ethics Review Board of Tilburg University. All participating parents will provided written informed consent for their own and their child’s participation, in accordance with the Declaration of Helsinki. Supporting materials, including the research proposal submitted for ethical review, the information letters for parents and teachers, and the informed consent form, are available in the supporting information (see S2 File). To protect the privacy of participating children and their parents, all shared data will be de-identified and stored in a secure repository (TiU Dataverse). Data will not be openly accessible but can be obtained upon reasonable request. Researchers who wish to access the data must submit a research proposal that falls outside the scope of the original research line, acknowledge the data source, and sign a data-sharing agreement. The company associated with one of the authors (m-Path Software) had no role in the study design, data collection and analysis, decision to publish, or preparation of the manuscript.

#### Timeline.

Participant recruitment will start in August 2025 and is expected to be completed by October 3, 2025. Intake interviews—including eligibility screening, explanation of the study procedures, and digital informed consent—will take place between September 1 and October 3, 2025, via scheduled video calls. Baseline assessments (T1), including home visits, parent questionnaires, and child interviews, will occur between September 15 and October 17, 2025. The intervention is scheduled to begin in the week of October 20, 2025, and will continue for 18 sessions through the week of March 9, 2026. Posttest assessments (T2), including follow-up home visits and questionnaires, will be conducted between March 16 and April 17, 2026. This timeline ensures a 5-week pretest period, an 18-week intervention period, and a 5-week posttest window. Study results are expected to be available by September 2026 and will be submitted for publication, presented at conferences, and reported in ClinicalTrials.gov.

### Intervention

#### Incredible Years Small Group Dinosaur Child Program.

The intervention group will receive the IY Small Group Dinosaur Child Program, a structured, manualized cognitive-behavioral intervention originally developed to support young children (ages 3–8) with conduct problems [20,21,24]. The program is designed to enhance emotional regulation, prosocial behavior, and problem-solving abilities through developmentally appropriate, interactive group-based sessions. Although initially developed for children with externalizing difficulties, it is now widely applied in broader populations, including children with internalizing difficulties such as social-emotional or attentional challenges [33]. In this study, the intervention will target children aged 4–8 years who exhibit elevated levels or (sub)clinical levels of conduct problems.

The program will be delivered in ten small groups, each consisting of 5–6 children. Each group will be facilitated by one certified group leader, using the Dutch translation and adaptation of the original IY protocol. Sessions will be held weekly for 18 weeks, with each session lasting approximately two hours. The curriculum will include storytelling with puppets, video modeling, role-play exercises, group discussions, and cooperative games. These elements are intended to foster emotional awareness, frustration tolerance, interpersonal problem-solving, and socially appropriate behavior. Parents in the intervention group will not receive a parallel parent training during the study period.

All groups will be led by one of six certified IY group leaders. Four of these professionals will be licensed child therapists affiliated with Psychologenpraktijk Timmers or Stichting Kumbaya, and two will be affiliated with Tilburg University. Prior to the start of the trial, all trainers will have completed the official IY certification process, which includes delivery of a full intervention cycle and a successful video-reviewed evaluation of fidelity and delivery quality.

#### Control condition.

Participants assigned to the control condition will be placed on a waitlist and will not participate in any structured group-based intervention during the study period. They will retain access to standard care and community-based services as needed, but will not receive any elements of the IY program during the data collection phase. Information on additional support received will be systematically collected via parental questionnaires.

After completion of the posttest assessment (T2), families in the control group will be offered the opportunity—on a voluntary basis—to participate in the IY Dinosaur Program. This post-trial intervention will be delivered by the same certified group leaders and institutions involved in the study (Tilburg University, Psychologenpraktijk Timmers, or Stichting Kumbaya), but will not be part of the research protocol. This design allows for a controlled comparison of intervention and non-intervention conditions, while ensuring equitable access to support after study completion.

#### Fidelity monitoring.

To ensure high-fidelity implementation, group leaders will follow a standardized session protocol and complete adherence checklists after each session. Fidelity will be further supported through regular supervision meetings with certified IY consultants. Prior to the start of the trial, all group leaders will have completed the formal IY certification process, including a video-reviewed delivery of the full program. Any deviations from the protocol will be documented and reported in the final study manuscript.

### Moderators

To explore individual variability in response to the intervention, several child-level moderators will be assessed prior to the start of the intervention (T1). These include emotional sensitivity, temperament traits, general sensitivity, and executive functioning. In addition, fluctuations in daily emotional functioning will be captured through ILD. These moderators will be examined as potential predictors of differential treatment effects.

#### Child temperament.

Child temperament will be assessed using the Child Behavior Questionnaire – Very Short Form (CBQ-VSF), a widely used parent-report instrument [34]. The CBQ-VSF contains 36 items rated on a 7-point Likert scale ranging from 1 (“extremely untrue”) to 7 (“extremely true”). Items cover multiple dimensions of temperament; in the current study, the Negative Affectivity subscale (e.g., “My child gets quite frustrated when prevented from doing something s/he wants to do”) will be used as a moderator. A composite score will be calculated as the mean of the subscale items. The CBQ-SF has demonstrated good internal consistency and construct validity in prior studies [35].

#### General child sensitivity.

The Highly Sensitive Child – Parent Report (HSC-PR) is a 12-item parent questionnaire that assesses environmental sensitivity in children [36]. Items are rated on a 7-point scale (1 = “not at all” to 7 = “very much”). A sample item is: “My child notices subtle smells or sounds that others do not.” Total scores will be calculated by averaging all items, with higher scores indicating greater sensitivity. The HSC-PR has shown good reliability and factor structure in recent studies [37].

#### Child emotional variability.

Emotional variability will be operationalized using parent–child dyadic daily assessments collected via the m-Path app [26]. Each evening, parents and children will complete a short diary survey including 2–3 emotion-related items (e.g., “Did your child experience strong emotions today?”) on a 5-point scale (1 = “not at all” to 5 = “very much”). Variability will be calculated based on within-person standard deviations, and changes over time will be explored using a moving window approach [28].

### Outcome measures

This study includes both group-level outcomes, assessed through pre- and post-intervention surveys, and micro-level measures, assessed through daily diaries, to evaluate the effectiveness of the Dinosaur Child Program across emotional, behavioral, and cognitive domains. Outcomes are collected via questionnaires from three informants (parents, teachers, and children), and supplemented by daily parent–child dyadic daily diary reports. Measures are aligned with the three main research questions. Primary outcomes are used to assess intervention effects at the group level (RQ1), while secondary outcomes capture dynamic emotional and behavioral processes within children (RQ2) and their families (RQ3).

#### Parent-reported outcomes.

***Parenting behavior (Explanatory outcome; RQ1).*** Parenting practices will be measured using the Parenting Practices Interview (PPI) [38]. The PPI includes 73 items rated on a 6-point Likert scale (1 = “never” to 6 = “always”) and covers domains such as positive involvement, inconsistent discipline, and harshness. A sample item is: “When your child misbehaves, how often do you give up trying to discipline him/her?”. Subscale scores will be used to explore potential changes in parenting behavior. Although parents are not enrolled in a formal parenting program, those whose children receive the Dinosaur intervention are indirectly exposed to parenting principles from the IY program. Through weekly letters, reading assignments, and homework exercises derived from the parent book used in the IY parent training, caregivers are encouraged to apply positive parenting strategies at home. The PPI was specifically developed to assess parenting behaviors targeted by the IY parent intervention

***Child externalizing behavior (Primary outcome; RQ1).*** The Child Behavior Checklist (CBCL) will be used to assess children’s behavioral and emotional problems from the parent’s perspective [39]. The CBCL includes 113 items rated on a 3-point scale (0 = “not true”, 1 = “somewhat true”, 2 = “very true”). The Externalizing Problems composite will serve as the primary indicator of behavioral change. To complement this, the Eyberg Child Behavior Inventory (ECBI) will be administered [40]. The ECBI consists of 36 items (e.g., “Refuses to go to bed”) rated for both frequency and problem severity.

***Child social behavior (Primary outcome; RQ1).*** Social competence will be measured using the Social Competence Scale – Parent version (P-COMP) [41]. This 12-item scale uses a 5-point Likert format (1 = “not at all” to 5 = “very well”) to evaluate skills like cooperation, self-control, and empathy. A sample item is: “How well does your child get along with other children?”.

***Executive functioning (Primary outcome; RQ1)***. Parents will complete the Behavior Rating Inventory of Executive Function, Second Edition– Parent form (BRIEF-2) [42,43]. This version includes 60 items rated on a 3-point Likert scale (1 = “never”, 2 = “sometimes”, 3 = “often”) and assesses executive functioning in daily life at home. A sample item is: “Has trouble remembering things, even for a few minutes.” The Global Executive Composite (GEC) score will be used at the primary outcome. The BRIEF-2 has demonstrated strong psychometric properties in both clinical and normative samples [44].

***Child language behavior (Primary outcome; RQ1).*** The Children’s Communication Checklist – Second Edition, Dutch version (CCC-2-NL) [45,46] will be used to assess the child’s communicative/language functioning from the perspective of the parent or caregiver. The CCC-2-NL consists of 70 items covering structural language skills (such as syntax and semantics) as well as pragmatic aspects of communication (e.g., inappropriate initiation, use of context, nonverbal communication). Items are rated on a 4-point scale (0 = “less than once a week or never” to 3 = “several times a day or always”), providing standardized composite scores to identify potential communication difficulties. The General Communication Composite (GCC) derived from the CCC-2-NL will serve as the primary indicator of change in child communicative behavior.

#### Teacher-reported outcomes.

***Child externalizing behavior (Primary outcome; RQ1).*** The Teacher’s Report Form (TRF) will be used to assess behavioral functioning in the school setting [39]. The TRF mirrors the CBCL and includes 120 items with the same 3-point scale. The Externalizing composite score will be used as a primary outcome.

***Child social behavior (Primary outcome; RQ1).*** Teachers will also complete the Social Competence Scale – Teacher version (T-COMP) [47]. This version includes items similar to those in the parent version and evaluates the child’s social functioning at school. T-COMP scores will be analyzed alongside parent reports to assess cross-contextual consistency in social competence.

***Child executive functioning (Primary outcome; RQ1).*** Teachers will complete the Behavior Rating Inventory of Executive Function, Second Edition – Teacher Form (BRIEF-2) [42,43]. This version contains 61 items, also rated on a 3-point Likert scale, and evaluates the child’s executive functioning in the school setting, including classroom behavior, task focus, and emotional regulation. The Global Executive Composite (GEC) score will be used to parallel the parent-reported outcome and enable comparison across contexts.

#### Child-assessed outcomes.

***Emotional understanding (Primary outcome; RQ1).*** Children’s emotional awareness will be assessed using the Wally Feeling Test [48], a structured task in which children identify and explain emotions depicted in cartoon vignettes.

***Problem-solving skills (Primary outcome; RQ1).*** Children will complete the Wally Problem Solving Test [49], a structured measure in which social dilemmas are presented in an illustrated format. Children are asked to generate possible solutions for each scenario. Responses are coded for quality and diversity, providing insight into cognitive-behavioral competencies such as perspective-taking, emotional regulation, and flexible problem solving—key targets of the intervention.

#### Daily diary-based outcomes.

***Emotional variability and behavior problems (Secondary outcomes; RQ2).*** To capture within-person variability in emotional and behavioral functioning, daily diary surveys will assess both emotional functioning and behavior problems, completed each evening by the parent–child dyad using the m-Path app [26]. Emotional variability will be measured using a set of seven momentary emotion items derived from the Positive and Negative Affect Schedule for Children (PANAS-C) [29] and the original PANAS [30]. Children will indicate how they felt “at the moment” on a 7-point scale ranging from 1 (*not at all*) to 7 (*very much*), for the emotions proud, happy, calm, ashamed, sad, angry, and tense. To enhance developmental appropriateness and alignment with the Dinosaur Child Program, each response option is accompanied by a visual cue: a small-to-large image representing the intensity of each specific emotion, consistent with the emotion cue cards used during the intervention. Behavior problems will be assessed with three items reflecting hostility-related externalizing behaviors, adapted from the externalizing spectrum framework [31]. These include losing one’s patience, saying something mean to someone, and being angry or aggressive towards someone. Responses will be recorded on a 5-point Likert scale ranging from 1 (*not at all*) to 5 (*very often*), allowing for sensitive detection of daily fluctuations in child behavior over time.

***Parent–child affective dynamics (Secondary outcomes; RQ3).*** To examine daily relational dynamics between parents and children, both members of the dyad independently complete a daily diary assessing shared emotional moments, negative interactions, emotion regulation, and time spent together. These items were adapted from validated measures of momentary relationship quality [32] and reflect shared emotional experiences, conflict-related emotions, and individual efforts at emotion regulation. This dyadic structure allows for the analysis of affective synchrony, divergence, and co-regulatory processes, which are central to understanding how the intervention impacts family functioning over time. Parents report whether they experienced nice moments with their child (“I had some nice moments with my child today.”) and whether they felt angry toward their child (“I got angry at my child today.”). These items are rated on 5-point Likert scales using either an intensity format (1 = *not at all* to 5 = *very much*) or a frequency format (1 = *not at all* to 5 = *very often*). In addition, a contextual control item is included to assess the amount of parent–child contact: “How many hours were you with your child today (excluding sleep time)?” (ranging from 0 to 24 hours). Children complete a mirrored set of items: they report whether they had nice moments with their parent, whether they got angry at their parent, how difficult it was to behave well, and what they did to manage their emotions if they felt angry. The regulation item includes a multiple-choice question offering strategies that are taught during the Dinosaur Child Program (e.g., taking deep breaths, doing the “turtle pose,” or thinking of something fun), along with an open-ended “other” option. Ratings use the same Likert formats as in the parent version to ensure comparability.

By collecting matched daily reports across 20 weeks of measurement, this dyadic ILD approach enables rich time-series analyses of both shared and diverging perceptions within the family. It allows the study to examine not only whether parent–child dynamics improve overall, but also whether these improvements are co-experienced and co-regulated — for example, whether decreases in child-reported anger correspond with reductions in parent-reported conflict, or whether increases in positive moments are felt mutually or asymmetrically. The inclusion of contextual time data enables the control of fluctuations in contact intensity, helping to interpret changes in affective dynamics relative to daily routines and caregiving structures.

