By collecting daily data on emotions, behaviors, and parent–child interactions, the ILD design not only identifies day-to-day variability but also provides insight into emotional sensitivity, behavioral adaptation, and relational patterns over time. Grounded in the Environmental Sensitivity Framework, the study operationalizes emotional sensitivity as moment-to-moment fluctuations in negative affect prior to the intervention, based on empirical indicators derived from daily diary reports. This framing allows us to explore whether children with higher baseline sensitivity respond differently to the intervention. Beyond identifying individual variability, daily diary data offer a window into potential mechanisms of change. Since interventions such as the Dinosaur Child Program aim to influence not only behavior but also emotion regulation and relational dynamics, it is crucial to understand how these processes unfold in the flow of everyday life. By tracking moment-to-moment affective and interpersonal shifts, we can reveal dynamic pathways of change, such as improved co-regulation or reduced emotional escalation. This process-level insight supports a shift from outcome-based evaluation to more personalized, mechanism-informed intervention strategies. Finally, the study examines how family micro-dynamics contribute to intervention outcomes. Because children’s behavior emerges through daily caregiver interactions, ILD enables analysis of these dynamic exchanges over time. Understanding real-life family processes underlying intervention effects is essential for advancing personalized child mental health care and tailoring support to individual needs the field of personalized child mental health care.

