### Study aim and research questions

The overarching aim of this study is to evaluate the effectiveness of the Dinosaur Child Program in reducing externalizing behavior and improving emotional and social functioning in children aged 4–8. Furthermore, the study aims to explore individual variability in intervention response and real-time parent–child dynamics using the daily diary methodology.

Specifically, the following research questions and hypotheses are addressed:

1. **Does participation in the Dinosaur Child Program lead to greater improvements in children’s emotional, social, and cognitive functioning, and reductions in externalizing behavior compared to a waitlist control group?**

*H1*: We hypothesize that children in the intervention group will show significantly more improvement in teacher- and parent-reported social, emotional, and cognitive/linguistic competencies, and significantly greater reductions in externalizing behavior than children in the control group.

2. **Does the intervention lead to reduced emotional variability and fewer daily behavior problems, as captured through daily diary methodology?**

*H2*: We hypothesize that children in the intervention group will exhibit fewer and less intense fluctuations in negative affect (controlled for mean level changes) and fewer moments of defiance, tantrums, or other behavior problems across the day, compared to the control group.

3. **Does the intervention alter day-to-day parent–child dynamics by reducing children’s experience of negative affect and promoting shared positive affect in interaction with their parents?**

*H3*: We hypothesize that children in the intervention group will show fewer escalations of negative affect and more intense shared positive moments with their parents than those in the control group. These effects are expected to be most pronounced in children who show higher baseline emotional sensitivity, operationalized as greater moment-to-moment fluctuations in negative affect prior to the intervention.

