#### Hypothesis 2: Daily variability and behavior problems (ILD-based).

To examine whether the intervention reduces children’s daily emotional variability and behavior problems, multilevel time-series analyses will be conducted on daily parent–child diary data. Daily reports will include ratings of negative affect (e.g., irritability, sadness) and behavior problems (e.g., defiance, tantrums). Repeated observations will be modeled as nested within individuals to capture both group-level trends and within-person variability over time. Fixed effects for time, group, and their interaction will be included to test for differential change trajectories across conditions. In addition, moving window techniques will be employed to capture changes in intra-individual fluctuations and identify evolving temporal patterns of variability throughout the intervention period.

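### H2 and the H3 moderator concern fluctuation in negative affect, but the measurement sections give conflicting item sets and scales and never tie the score to negative affect

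*Protocol article*

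**What the plan says.** **Hypotheses.** In the Protocol article, Study aim and research questions, H2 predicts "fewer and less intense fluctuations in negative affect (controlled for mean level changes") in the intervention group. H3 expects its effects to be strongest in children with higher baseline emotional sensitivity, "operationalized as greater moment-to-moment fluctuations in negative affect prior to the intervention". The Introduction agrees: "the study operationalizes emotional sensitivity as moment-to-moment fluctuations in negative affect prior to the intervention".

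**Outcome.** Under Daily diary-based outcomes, "Emotional variability will be measured using a set of seven momentary emotion items", answered on a 7-point scale "for the emotions proud, happy, calm, ashamed, sad, angry, and tense". The section names no negative-affect subset and gives no rule for combining items.

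**Moderator.** Under Moderators, Child emotional variability, parent and child "complete a short diary survey including 2–3 emotion-related items" on a 5-point scale. The example is "Did your child experience strong emotions today". Variability is the within-person standard deviation.

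**Analysis.** The Hypothesis 2 section begins "To examine whether the intervention reduces children’s daily emotional variability and behavior problems". Its next sentence describes the ratings as negative affect and gives irritability and sadness as examples.

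**The concern.** One construct is described in several places, and the descriptions differ in valence, item set and response scale. Two analyses depend on which description is followed.

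- **H3 moderator.** H3 concerns children whose negative affect swings most before the program. A standard deviation taken over items about strong emotions of any kind also rises with joyful or proud peaks. A child with many such peaks counts as variable on that measure but not under H3.
- **H2 outcome.** If the seven items were combined, change in negative-affect fluctuation would be mixed with whatever happens to proud, happy and calm. H3 itself expects more intense shared positive moments. That does not show that positive-affect fluctuation will rise, but it is a reason not to assume that the two valences move together.

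Until one score is fixed, it could also be chosen after seeing which version shows an effect.

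**Working it through.** **1. The sections side by side**

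| Place in the Protocol article | Valence | Items | Scale |
|---|---|---|---|
| Introduction; H2; H3 moderator | negative only | not listed | not given |
| Moderators, Child emotional variability | none in the example item | 2–3, one example shown | 5-point |
| Daily diary-based outcomes | mixed: 3 positive, 4 negative | 7, all listed | 7-point |
| Hypothesis 2 analysis | negative in the description of ratings | irritability and sadness as examples | not given |

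Item number and scale disagree between the second and third rows. Irritability in the fourth row is not in the list in the third. Only the second row comes with a variability statistic, and its example item does not isolate negative affect.

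**2. The protocol's own figures**

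The point disputes no stated number. The between-person sample sizes reproduce: an exact two-sample t-test (two-sided 0.05, power 0.80) gives 64 per group at d = 0.5 and 26 at d = 0.8. The 140 diary time points follow from 7 × 20. The diary power claim (above 80% at β = 0.005) cannot be checked because no variance components are given.

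**3. What pooling could do to H2 (illustration)**

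Assumed, not taken from the protocol: variability is computed per item and averaged; an effect d applies to each of the four negative items; items correlate equally at r; two-sample t-test, two-sided 0.05. The 60 per arm is the planned sample size.

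The standard deviation of a mean of k such items is √((1 + (k − 1)r)/k). At d = 0.4 and r = 0.5:

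- Divisor for four items: √(2.5/4) = 0.791. Divisor for seven: √(4/7) = 0.756.
- Four negative items: 0.4/0.791 = 0.51, power 0.78.
- All seven, no effect on positive items: (4 × 0.4/7)/0.756 = 0.30, power 0.38.
- All seven, positive-item variability rising by 0.2: ((1.6 − 0.6)/7)/0.756 = 0.19, power 0.18.
- All seven, positive-item variability falling equally: 0.4/0.756 = 0.53, power 0.82.

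Over d = 0.3–0.5 and r = 0.3–0.7, power is:

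| Score and scenario | Power |
|---|---|
| Four negative items | 0.46–0.98 |
| Seven items, only negative responds | 0.19–0.69 |
| Seven items, positive variability rises by 0.2 | 0.08–0.40 |
| Seven items, both fall equally | 0.47–0.99 |

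**4. Second check, by simulation**

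Assumed: 60 per arm, 126 days, a 20% fall in the SD of the negative-affect factor, between-person log-SD 0.35, item noise SD 0.8, and a correlation between negative and positive factors of −0.2 to −0.8. Seven items were pooled in three ways (raw mean, reverse-keyed mean, average of item SDs).

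| Score | d | Power |
|---|---|---|
| Four negative items | about 0.59 | about 0.90 |
| Seven, only negative responds | 0.34–0.47 | 0.45–0.72 |
| Seven, positive fluctuation also falls 20% | 0.57–0.66 | 0.87–0.95 |
| Seven, positive fluctuation rises 20% | 0.05–0.23 | 0.06–0.23 |

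Both methods agree: the loss depends wholly on how positive-affect fluctuation behaves.

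**The case against.** **The seven items may never be pooled.** A reader might infer from the outcome section that the stated H2 measure is a seven-emotion score, so that dilution or cancellation is built in. The text does not support that. It lists what the diary collects and never says the items are combined, and the H2 analysis section describes the ratings as negative affect. This stands: dilution is a risk of an unfixed score, not a consequence of the plan.

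**The Moderators section does not name itself as the H3 moderator.** Its overview lists emotional sensitivity and then, additionally, daily emotional fluctuation, and only one of the two or three items is shown. This stands in part. The unseen items might be negative. However, this is the only moderator section describing a diary measure, and it does not mention negative affect.

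**The power figures are not those of the planned analysis.** They compare one score per child by t-test, whereas the plan is multilevel time-by-group models with moving windows. This stands; the figures show direction and rough scale only.

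**Scoring belongs in an analysis plan.** This is fair for a missing detail, and such a plan is not shown. It does not answer the disagreement within the article on items and scale, since any later document must override one of the printed descriptions.

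**Conclusion.** The mismatch holds as a matter of text. H2 and the H3 moderator are about negative affect, while the Moderators and outcome sections describe two different diary measures of emotional variability, neither tied to negative affect, and the H2 analysis section cites an emotion outside the item list.

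The firmer consequence is for H3. If the Moderators measure is used as its example suggests, children are ranked on general emotionality. For H2 the consequence is conditional: it needs all seven items to be pooled and positive-affect fluctuation not to fall alongside negative. Under those assumptions the base case drops from power 0.78 to 0.38; if both fall, little or nothing is lost. It cannot be concluded that the plan as written will miss the H2 effect.

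This should be corrected before the diary data are analysed. It concerns secondary outcomes and a moderator, and leaves the RQ1 primary results and the stated sample sizes unaffected.

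**What to change.** Reconcile the Child emotional variability, Daily diary-based outcomes and Hypothesis 2 sections so that they say the same thing:

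- The daily negative-affect score is the mean of ashamed, sad, angry and tense, on the 7-point scale.
- The H2 outcome is the within-person variability of that score; the H3 moderator is the same quantity in the baseline period.
- Variability of proud, happy and calm is reported separately as exploratory.
- The strong-emotions item is used for neither the H2 outcome nor the H3 moderator.
- The examples in the Hypothesis 2 section are drawn from the items actually collected.

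The cost is wording in three sections. All seven items are already planned for collection, so there is no added burden on families. What is given up is a single all-emotion index.
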